#### 5. HYPOTHESES

**Primary Hypothesis:** Treatment of pre-school children with an acute episode of wheezing symptoms with 5 days of azithromycin will resolve their symptoms sooner.

**Secondary Hypotheses:** Treatment of pre-school children with acute wheezing symptoms with 5 days of azithromycin will: a) cause these children to use less rescue  $\beta_2$  agonists than those treated with placebo; and b) allow these children to remain free of subsequent wheezy episodes longer than those treated with placebo.

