***Safety monitoring committee and termination policy:*** Adverse events will be actively monitored up to 30 days after the last of Azithromycin was given (day 5). Any child who develops symptoms consistent with adverse effects to azithromycin as evidenced by diarrhea or loose stools, nausea, abdominal pain, and vomiting (common side effects), symptoms of allergic reaction (hives), changes in mood or behaviour, arrhythmia/tachycardia will result in the review of their case by a safety monitoring committee consisting of a pediatric pulmonologist, allergist, and general pediatrician. The committee will review the case and decide whether to break the code and/or terminate the study based on the particulars of the case. If upon review there are concerns about the patient, the code would be broken and the randomization drug discontinued. The panel may consider terminating the study if there are profound adverse effects that would reflect concerns for all children.

***Sample Size and Minimal Clinically Important Difference:*** The telithromycin in acute adult asthma study demonstrated a 50% reduction in asthma symptoms among those using telithromycin (16% asthma symptoms in the placebo group versus 8% in the telithromycin group). We have used this data to estimate the magnitude of effect for our sample size calculations (a 50% decrease in the number of days to symptom resolution). Enrolment of 110 children per treatment arm per first-time versus previous wheeze (total 440), using a one-way ANOVA, will provide 80% power to detect at the .05 level, a 1.18 day

differences in the two treatment groups. This calculation assumes a conservative standard deviation of 6 days in symptoms duration and a 10% loss to follow-up. For the planned sub-group analysis of first-time versus previous wheeze, we have sufficient power to detect a 1.36 day difference between the azithromycin and placebo groups (*Appendix M – Power Calculation*). We think that a reduction in the duration of symptoms by one day or more is likely to be considered meaningful because of its implication for a child missing daycare or school, or parents missing work.

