**Statistical Analysis:** The baseline variables in the two groups will be compared overall and by enrolment center in terms of means, standard deviation, and range, and as appropriate, median, inter-quartile range, percentages and 95% confidence intervals. Imbalances between treatment groups for key baseline variables such as age, gender, duration of illness, presence of atypical bacteria, use of ICS or oral corticosteroids, and baseline clinical severity will indicate the need for an adjusted analysis. We will also include an interaction term in the analysis (drug X presence or atypical bacterial infection) to determine if azithromycin has a different degree of effectiveness among those with atypical bacteria present. Furthermore, for each response variable, we will perform an exploratory adjusted analysis incorporating enrolment center as a factor to ensure that unmeasured differences between enrolment centers do not bias our results. The primary outcome, time to symptom resolution, will be assessed for normality of distribution by the Wilk Shapiro Test and, if necessary, will be transformed to yield suitable distributions or Kruskal Wallis (non parametric ANOVA analogue) will be used to test the main hypothesis. If the one way ANOVA is significant, then, a-priori decided comparisons (placebo versus azithromycin in first-time wheezing children and placebo versus azithromycin in children with a prior wheeze history) will be tested via Tukey's Honest significant differences procedure. If an adjusted analysis is necessary, we will use an Analysis of Covariance model incorporating those baseline factors which are imbalanced between treatment groups and any other variable that is thought to be of clinical relevance. An adjusted analysis will be performed in the event that co-intervention numbers (such as ICS or oral corticosteroid use) between the groups are not comparable. We also plan to perform a sub-group analysis to detect clinically significant differences in the each of the two wheezing sub-groups. Linear regression will be used to analyze  $\beta$ -agonist use during the 21 day follow-up period and Cox regression modelling will be used to analyse the time to next disease exacerbation.

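### The one-way ANOVA named as the test of the main hypothesis does not match the single azithromycin-versus-placebo question; with the Tukey step that follows, it can only be run as a four-cell omnibus test

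*Protocol*

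**What the plan says.** Section 5 (Hypotheses) states the primary hypothesis as a drug effect in all enrolled children: "Treatment of pre-school children with an acute episode of wheezing symptoms with 5 days of azithromycin will resolve their symptoms sooner".

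The Statistical Analysis paragraph of section 6 says that time to symptom resolution will be checked for normality and then transformed if necessary, or that "Kruskal Wallis (non parametric ANOVA analogue) will be used to test the main hypothesis". It goes on: "If the one way ANOVA is significant, then, a-priori decided comparisons (placebo versus azithromycin in first-time wheezing children". The second planned comparison is the same contrast in the other history group, and the paragraph names the method for both: "placebo versus azithromycin in children with a prior wheeze history) will be tested via Tukey's Honest significant differences procedure". An ANCOVA is planned only if baseline factors or co-interventions are imbalanced, and the centre-adjusted analysis is labelled exploratory.

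The Sample Size paragraph ties the calculation to the same test: "Enrolment of 110 children per treatment arm per first-time versus previous wheeze (total 440), using a one-way ANOVA". It claims 80% power at the 0.05 level for a difference of 1.18 days, which it describes as lying between two treatment groups. The inputs are 10% attrition and an SD of 6 days; on the SD it says: "This calculation assumes a conservative standard deviation of 6 days in symptoms duration". Randomisation is stratified by site and by first versus previous wheeze.

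The groups entering the one-way ANOVA are not listed anywhere in the text at hand.

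**The concern.** Tukey's procedure compares pairs of the groups that entered the ANOVA. Placebo versus azithromycin among first-time wheezers, and the same among prior wheezers, are such pairs only if the groups are the four drug-by-history cells. The sizing per arm per history group fits that.

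A four-cell one-way ANOVA has 3 degrees of freedom, and its null is that all four means are equal. It is rejected if azithromycin works, but also if first-time and repeat wheezers simply recover at different speeds. Randomisation gives no protection, because wheeze history is part of the grouping factor and is not balanced out of it. Spreading the test over three degrees of freedom also costs power when the drug effect is the same in both history groups. On this reading the overall drug effect of section 5 is never tested as one contrast.

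At stake is whether a significant primary test says anything about the drug, and how likely the trial is to detect a real effect.

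**Working it through.** **Inputs.** From the Sample Size paragraph: 4 cells of 110, 10% loss (110 × 0.9 = 99 per cell, 396 in all, 198 per arm), SD 6, alpha 0.05, taken as two-sided because the protocol does not say. The recovery difference between history groups, h, is not given; 0 to 3 days is an assumption.

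**The plan's own figure.** For two arms at 80% power the detectable difference is about (1.960 + 0.842) × 6 × √(2/n).
- n = 220: 2.802 × 6 × 0.0953 = 1.60 days.
- n = 198: 2.802 × 6 × 0.1005 = 1.69 days.

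The stated 1.18 days is not reproduced by either, nor by the four-cell test, which needs a uniform effect of 1.90 days (N = 440) or 2.00 days (N = 396). That is a separate matter; 1.69 days serves as the yardstick below.

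**Omnibus test, no drug effect.** The non-centrality is λ = 99 × Σ(μᵢ − μ̄)²/36, with 3 and 392 df. With a history difference h only, each cell lies h/2 from the mean, so λ = 99 × 4 × (h/2)²/36 = 2.75h².

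| h (days) | λ | P(omnibus significant) |
|---|---|---|
| 0 | 0 | 5% |
| 0.5 | 0.69 | 9% |
| 1 | 2.75 | 25% |
| 2 | 11.0 | 80% |
| 3 | 24.75 | 99% |

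Kruskal-Wallis over the same cells behaves alike. With gamma durations (CV 0.75, means 8 and 10 days by history, no drug effect; all assumed), it rejected in 59% of simulated trials.

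**What the Tukey step does.** The full sequence was simulated 40,000 times per setting with normal data. With no drug effect, a significant omnibus test plus at least one significant placebo-versus-azithromycin pair occurred in 1.8%, 1.9%, 1.9% and 2.0% of trials at h = 0, 1, 2 and 3.

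**Power for a uniform drug effect d, with h = 0.** The non-centrality has the same form, λ = 2.75d².

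| d (days) | λ | 1-df contrast | Omnibus | Omnibus plus a Tukey drug pair |
|---|---|---|---|---|
| 1.69 | 7.85 | 80% | 64% | 47% |
| 1.18 | 3.83 | 50% | 34% | 21% |

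With h above 0 the omnibus test rejects more often (78% at h = 1, d = 1.69), but the excess is due to history: the last column stays at 47% for d = 1.69.

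**The two-arm reading.** With two groups the ANOVA is the 1-df test in the table and the inflation disappears. Tukey then has a single pair, so neither named within-group comparison can come from it.

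**The case against.** **The four-cell structure is inferred.** The Study Overview calls the trial two-arm, the Sample Size paragraph speaks of two treatment groups and gives the sub-group analysis its own figure (1.36 days), and the power appendix, which might name the groups, is not at hand. This stands. A reader might infer that the protocol definitely specifies an omnibus primary test; it supports only that the written sequence can be run in no other way.

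**Tukey protects the drug claim.** This also stands. A reader might take 25%, 80% and 99% as rates of false drug claims. They are not: the specified follow-ups hold such claims near 2%. The larger figures matter only if the omnibus p-value is reported as the drug result, which the wording permits because it attaches the main hypothesis to that test.

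**The protocol does not predict a recovery difference.** The background and randomisation text on the two history groups concerns mainly whether they respond differently to treatment. It does not establish that they recover at different speeds without it.

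**Sub-group analyses are not all gated.** A reader might infer that on the two-arm reading a non-significant overall test blocks any within-group analysis. The same paragraph also plans a sub-group analysis in each wheezing group without that condition, so only the Tukey route is gated.

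**The omnibus test is not always weaker.** For a 2.4-day effect confined to one history group, λ = 99 × 4.32/36 = 11.88 and its power is 83%, against 51% for the 1-df contrast (average effect 1.2 days). That is a reason to keep a secondary look at heterogeneity. It does not make the omnibus test an answer to the overall question in section 5.

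**Conclusion.** The concern holds as a mismatch between the primary hypothesis and its stated test, and the text needs correcting on either reading. On the four-cell reading, the omnibus test can be significant from wheeze history alone (25% at an assumed 1 day, 80% at 2 days), and the overall drug effect is not tested as a single contrast. A uniform effect of 1.69 days has 64% power in the omnibus test and about 47% through the full sequence, against 80% for a single contrast. On the two-arm reading the inflation vanishes, but the Tukey comparisons cannot be produced.

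The figures rest on 99 evaluable per cell, SD 6, two-sided 0.05 and, apart from the Kruskal-Wallis example, normal data. The documents do not support saying that the plan as a whole inflates false drug claims; that follows only if the omnibus result is reported as the drug result.

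**What to change.** In Statistical Analysis, replace the one-way ANOVA/Kruskal-Wallis sentences with text to this effect:

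- The primary test is the 1-df azithromycin-versus-placebo effect from a model with treatment and wheeze history (the randomisation stratum), reported with its 95% confidence interval. If a rank method is needed, use one stratified by wheeze history, such as the van Elteren test.
- The two within-history drug effects come from a second model that adds the treatment-by-history interaction, because an additive model forces the same effect in both groups. They are secondary, follow a stated multiplicity rule, and do not depend on an omnibus test.

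In the Sample Size paragraph, state that power refers to the 1-df contrast and give the detectable difference for it.

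The 1-df test keeps its type I error for the drug at 5% whatever the history difference. The cost is a few sentences and a restated power calculation, with no added patients or data. The price is that the within-history comparisons are explicitly secondary.

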**Co-Interventions and Contamination:** Staff ED physicians will be asked not to treat enrolled patients with antibiotics. Otherwise physicians will be allowed to prescribe any treatment, in addition to the study drug and rescue SABA, they judge to be necessary (e.g. oral or inhaled corticosteroids). While treatment with corticosteroids has the potential to contaminate the effects of the study medication, given our study's randomized design, each treatment group will most likely have comparable numbers of patients treated with co-interventions. All medications (including duration and dosages) patients receive at enrolment and during follow-up will be documented. A letter will also be sent to the child's primary care physician at the time of enrolment detailing the nature of the study and that the child has been randomized to either azithromycin or placebo to be taken for 5 days in total.

**Data gathering and Patient Follow-up** (*Appendix H – Data quality & monitoring*)  
**Daily Symptom Diary:** Parents will be given a Ordinal Daily Symptom Diary with the following ordered categories: heart = 'no respiratory symptoms'; green star = 'mild respiratory symptoms'; yellow star = 'respiratory symptoms are worse than usual or more medication than usual was required'; red star = 'respiratory symptoms sufficiently severe to require an unscheduled visit to a physician or treatment with oral corticosteroids' or Blue star = in addition to one of the above and a cold or flu symptoms appear. Star stickers are to be provided to place in blue boxes each day of study syrup is provided. Parents will be

instructed to focus on any noisy breathing respiratory symptom (wheezing or whistling sounds), breathlessness with eating or speaking, shortness of breath after activity or exposure to cold, or persistent troublesome coughing. (*Appendix G – Ordinal Daily Symptom and Drug Dosing Diary*). This Ordinal Daily Symptom Dairy has been used in a prior study by PM with excellent parental and child compliance, and good discrimination in respiratory symptoms between treatment groups (Montelukast versus placebo).

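### The co-intervention rule does not exclude steroid use after the first study dose, so the adjusted treatment effect can be biased if azithromycin changes that use

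*Protocol*

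**What the plan says.** All places are in section 6 of the protocol.

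- **Statistical Analysis, the trigger.** "An adjusted analysis will be performed in the event that co-intervention numbers (such as ICS or oral corticosteroid use) between the groups" are found not to be comparable. No criterion for comparability and no time window are given.
- **Statistical Analysis, the model.** If adjustment is needed, "we will use an Analysis of Covariance model incorporating those baseline factors which are imbalanced between treatment groups and any other variable" judged clinically relevant. The second part of that list is not confined to baseline.
- **Statistical Analysis, baseline use.** Steroid use already appears among the key baseline variables: imbalance in "presence of atypical bacteria, use of ICS or oral corticosteroids, and baseline clinical severity will indicate the need for an adjusted analysis". The co-intervention sentence therefore covers something beyond baseline use.
- **Co-Interventions and Contamination.** ED staff are asked to withhold antibiotics. "Otherwise physicians will be allowed to prescribe any treatment, in addition to the study drug and rescue SABA, they judge to be necessary", with oral and inhaled corticosteroids as the examples. On timing: "All medications (including duration and dosages) patients receive at enrolment and during follow-up will be documented". The paragraph expects randomization to make co-intervention use similar in the two arms.
- **Daily Symptom Diary.** The worst category is defined as "respiratory symptoms sufficiently severe to require an unscheduled visit to a physician or treatment with oral corticosteroids".
- **Secondary Outcome.** Oral corticosteroid treatment for acute respiratory symptoms, after the first episode has resolved, is one of the two ways to have an exacerbation.

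**The concern.** Randomization protects comparisons adjusted for variables fixed before treatment. It does not make later variables comparable. A child whose symptoms persist would plausibly be more likely to receive a steroid, and the primary hypothesis is that azithromycin shortens symptoms. A between-arm difference in follow-up steroid use could then be a result of treatment. The rule treats it as a nuisance to be removed.

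The protocol's own definitions tie oral steroid treatment to outcome: it is one route to a red-star day and a component of the exacerbation endpoint. Because the rule acts only on imbalance, it is invoked more often when the drug does affect steroid use, which is when adjustment is unsafe. At stake is whether the adjusted figure still estimates the effect of assigning azithromycin.

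**Working it through.** The protocol states no figure on this point, so there is none to reproduce. The text settles whether the rule reaches follow-up use; simulation shows what follows if it does.

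**Step 1, reach of the rule.** Baseline steroid use is named separately, the co-intervention sentence has no time limit, and medications are recorded during follow-up. Nothing keeps post-dose use out of the model.

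**Step 2, steroid use driven by symptoms.** From the protocol: standard deviation 6 days; 220 children per arm less 10% loss = 198. All other inputs are assumptions.

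- Latent duration = 9 − 1.69 × arm + 3 × severity, with severity standard normal.
- Probability of a steroid = logistic(−2 + slope × (latent − 9)). Steroids have no effect of their own.
- Outcome = latent + normal error with SD 5.2. Total SD = √(3² + 5.2²) = 6.0.
- The 1.69 days is the difference detectable with 80% power: (1.96 + 0.84) × 6 × √(2/198) = 1.69.

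Results from runs of 20,000 children, where the unadjusted estimate is about −1.69:

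| Slope per day | Adjusted for steroid use | Shrinkage |
|---|---|---|
| 0 | −1.69 | 0% |
| 0.35 | −1.53 | 0.16/1.69, about 10% |
| 0.6 | −1.33 | 0.36/1.69 = 21% |
| 1.0 | −1.08 | 0.61/1.69 = 36% |

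At slope 0.35, steroid use was 15.9% on placebo and 10.0% on azithromycin. At trial size (396 evaluable) the 0.16-day shift compares with a standard error of 6 × √(2/198) = 0.60 days. Always adjusting lowers power from about 80% to 73%. Taking p < 0.05 as the trigger (an assumption), it fires in about 40% of trials.

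**Step 3, other causal structures.** 198 per arm, 3,000 replicates per scenario. Outcome = 8 + 6 × (0.6U + 0.8e) − 1 × arm + b × steroid, where U is severity. Placebo steroid use is 30% at average severity. The table varies the drug's odds ratio (OR) on steroid use, the steroid effect b, and whether U also drives steroid use. The trigger is chi-square p < 0.05.

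| Scenario | Unadjusted | Adjusted | Trigger fires |
|---|---|---|---|
| OR 1, b = 0, shared severity | −0.98 | −0.98 | 5% |
| OR 0.7, b = 0, shared severity | −0.99 | −0.80 | 28% |
| OR 0.5, b = 0, shared severity | −1.00 | −0.64 | 74% |
| OR 0.5, b = −1 day, shared severity | −0.87 | −0.64 | 75% |
| OR 0.5, b = −1 day, severity not shared | −0.88 | −1.01 | 83% |

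The last row can be checked by hand. Placebo odds are 0.3/0.7 = 0.429; halved they are 0.214, a probability of 0.176. Steroid use falls by 0.30 − 0.176 = 0.124, so the total effect is −1 + 0.124 = −0.88 days. Adjustment returns the direct effect, about −1, which is a different quantity and here a larger one.

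**The case against.** Four points count against a stronger reading.

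- **That the rule biases the estimate as such.** A reader might infer this. It does not: if the drug leaves steroid use unchanged, the two estimates agree (−0.98 and −0.98). Steroids given in the ED before the first dose cannot be caused by the drug and are legitimate covariates. The documents give neither rates nor timing of steroid use.
- **That the rule always adjusts a benefit away.** The last scenario moves the other way. The protocol's stated worry, active steroids masking the drug effect, belongs to the b = −1 cases, where the direction depends on whether severity also drives steroid use.
- **That the plan does not say which result decides.** This is only partly right. The Statistical Analysis paragraph assigns the main hypothesis to ANOVA, after transformation if needed, or Kruskal-Wallis, and nothing says ANCOVA replaces it. The SAP, which was not available, may rank the analyses. Still, the centre-adjusted analysis is called exploratory and the co-intervention adjustment is not.
- **That steroid use is the primary outcome.** It is one route to one diary category. Resolution is defined by three consecutive days in better categories, and a red day also arises from an unscheduled visit alone.

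These points limit the direction, size and certainty of the bias. They do not supply the missing limit to pre-dose use.

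**Conclusion.** The point holds in conditional form. The protocol commits to an adjusted analysis on a trigger that can be set off by follow-up steroid use, and does not keep that use out of the covariates. If azithromycin changes symptoms and hence steroid use, the adjusted effect can be biased: toward zero when steroid use mainly follows severity, possibly away from zero otherwise.

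Shrinkage ranged from 0% to about 36% under assumed inputs. The 10% figure belongs to one scenario and is not a forecast. Since the protocol regards one day as meaningful, the upper part of that range (0.36 days on a true 1.00, or 0.61 on 1.69) would matter; 0.16 days is small beside a standard error of 0.60. The finding does not show that the primary test is invalid or that an adjusted result would overrule it.

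**What to change.** In the Statistical Analysis paragraph, or in the SAP:

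1. State that the deciding comparison for the primary outcome is not adjusted for any treatment started after randomization.
2. Limit ICS and oral corticosteroid covariates to use recorded before the first study dose.
3. Tabulate later ICS and oral corticosteroid use by arm.
4. Label any analysis that adjusts for follow-up co-interventions as exploratory and not deciding the conclusion. The trigger need not be deleted if it leads only to such an analysis.

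The cost is wording. Sample size, visits and treatment are untouched. Item 2 requires that the enrolment record show whether a steroid came before or after the first dose; the data forms are not in the document, so this should be checked.

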***Allocation, randomization, and blinding of study treatment (intervention):***

***Randomization method:*** A 2 X 2 variable blocked randomization code (ranging between 4 and 8 per block), with stratification by study site and first versus previous episode of wheeze, will be produced by the Drug Development and Innovation Centre at the university of Alberta (DDIC) using random-number generating software. DDIC will produce the study packages, complete the block randomization, and number the bottles. The blinded and numbered study drug packages, in addition to the master code will be available to both study sites if de-blinding is required. Stratification by ‘history of wheeze’ will allow us to track the number enrolled into each sub-group, and ensure we achieve our targeted sample size for each one. We have included children with both first and prior episode of wheeze and powered our study to perform a sub-group analysis for these two groups. Macrolide therapy has been shown to be effective in both bronchiolitis and asthma; incorporating both populations into this study design may provide important insights into how these populations of patients might differ.

Children will be defined as first-time wheezer if they have never had symptoms of wheeze prior to this episode, the symptoms of wheeze have been occurring for < 1 month with no period without resolution of symptoms for greater than 1 week during that 1 month period. Resolutions of symptoms include absence of all respiratory symptoms including wheeze, cough, respiratory distress, and shortness of breath. Some illustrative examples: If the patient has had symptoms for greater than 1 month- these children would be considered a repeat wheezer. If the child has had symptoms of wheezing for 1 month but had a 1 week period without respiratory symptoms in that one month, and we are seeing them after the 1 week resolution period, these children would be also be considered a repeat wheezer. IF the child has had wheezing symptoms for 1 month but was never symptoms free for more than 1 week continuously, this child would be considered a first-time wheezer.

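### The trial is stratified on first versus previous wheeze partly to learn how the groups differ, but no stated analysis tests whether the azithromycin effect differs between them

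*Protocol*

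**What the plan says.** All places are in the Protocol, section 6 (Research Design), unless noted.

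- **Randomization method.** Allocation is "with stratification by study site and first versus previous episode of wheeze". The text says the investigators "powered our study to perform a sub-group analysis for these two groups", and adds that "incorporating both populations into this study design may provide important insights into how these populations of patients might differ". It also gives operational reasons for stratifying: counting enrolment in each group and reaching each target.
- **Sample Size.** The design is "Enrolment of 110 children per treatment arm per first-time versus previous wheeze (total 440), using a one-way ANOVA". The subgroup calculation quotes a detectable difference of 1.36 days between azithromycin and placebo, not between the two wheeze-history groups.
- **Statistical Analysis.** If the one-way ANOVA is significant, two comparisons follow by Tukey's procedure: "placebo versus azithromycin in first-time wheezing children and placebo versus azithromycin in children with a prior wheeze history". A further sentence reads "We also plan to perform a sub-group analysis to detect clinically significant differences in the each of the two wheezing sub-groups" and names no model. The one interaction stated is for another factor: "We will also include an interaction term in the analysis (drug X presence or atypical bacterial infection"), to see whether the drug works to a different degree when atypical bacteria are present.
- **Sections 4 and 5 (Objective, Hypotheses).** These pose drug-versus-placebo questions only.

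**The concern.** Section 3 (Background Literature) presents it as unsettled whether children with a first wheeze respond to treatment differently from those with earlier episodes. The randomization text takes this up as something the trial may illuminate. The null hypothesis for that question is that the drug effect is equal in the two strata.

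Each planned contrast has a different null: no drug effect in this stratum. Neither contrast, nor the pair together, tests equality. The protocol uses an interaction term for atypical bacteria but states none for its own stratification factor.

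What is at stake is interpretation. If one stratum reaches significance and the other does not, a reader will be inclined to conclude that azithromycin works in one type of wheezer only. That pattern is common when the effects are identical, and the stated plan supplies no estimate that would check the inference.

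**Working it through.** **Inputs.** From Sample Size: SD 6 days, 110 children per arm per stratum, 10% loss (so 110 × 0.9 = 99 evaluable per cell), 80% power, alpha 0.05. Assumed: two-sided tests, normal outcomes, and a four-cell one-way ANOVA (two arms by two histories), which the two Tukey comparisons imply. For four groups Tukey's critical |t| is about 2.58.

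**The plan's own figures.** Detectable difference = SD × √(2/n) × (1.96 + 0.84).
- Within a stratum: 6 × √(2/99) × 2.80 = 2.39 days; with 110 per cell, 2.27 days. The stated 1.36 days is not reproduced. Power at 1.36 days is 36% (99 per cell) or 39% (110).
- Overall: 1.69 days (198 per arm) or 1.60 days (220 per arm). The stated 1.18 days is not reproduced.

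That mismatch is a separate matter and the present point does not depend on it. If each stratum truly had 80% power, exactly one would be significant in 2 × 0.8 × 0.2 = 32% of trials with equal effects, using unadjusted tests.

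**Discordance under the stated procedure.** The standard error of a within-stratum difference is 6 × √(2/99) = 0.853 days. Ignoring the ANOVA gate, a stratum with true effect d is significant with probability p ≈ Φ(d/0.853 − 2.58). With equal effects in independent strata, exactly one is significant with probability 2p(1 − p). At d = 1.36: 1.36/0.853 = 1.595, p = Φ(−0.985) = 0.162, and 2 × 0.162 × 0.838 = 27.2%.

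Adding the gate by simulation (200,000 runs per setting, 99 per cell, equal mean duration in the two histories):

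| Common true effect | Tukey only, formula | ANOVA gate + Tukey, simulated | Interaction test at 0.05 |
|---|---|---|---|
| 0 days | – | 1.8% | 5.0% |
| 1 day | 14.7% | 13.9% | 5.0% |
| 1.36 days | 27.2% | 26.5% | 5.1% |
| 2.0 days | 48.3% | 47.5% | 5.0% |
| 2.39 days | 48.5% | 48.0% | 5.0% |
| 3.0 days | 28.8% | 28.6% | 5.0% |

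If mean symptom duration differs by 2 days between the histories, the gated figures change by at most 1.0 percentage point. With 110 per cell they are 15.5% at 1 day, 29.4% at 1.36 days and 45.5% at 2.39 days. At 1.36 days both strata are significant in 2.7% of trials, so among trials with any significant stratum 26.5/(26.5 + 2.7) = 91% show only one.

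**What an interaction term would deliver.** Standard error = 6 × √(4/99) = 1.21 days. The 95% half-width is 1.96 × 1.21 = 2.4 days. The difference in effects detectable with 80% power is 2.80 × 1.21 = 3.4 days. Power for a 1.36-day difference in effects is about 20%.

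**The case against.** A reader might infer that the protocol plans to judge differential response from the pair of within-stratum tests. It does not say so. The objective, the hypotheses and the power statement ask only whether the drug beats placebo, and pre-specified, multiplicity-adjusted contrasts are valid answers to whether it works in each stratum. The remark about how the populations might differ is a soft, exploratory rationale. All of this stands, and it limits the point to a gap and the misreading it invites.

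A reader might also quote the discordance of unadjusted t-tests at 0.05, which is higher at smaller effects: 34% at 1 day and 46% at 1.36 days. Those rates belong to a procedure the protocol does not fix, since the further subgroup sentence names no test. The gated Tukey figures are the right ones. Nor is discordance a type I error rate, because no rule in the protocol declares heterogeneity from it. With no drug effect it is about 2%, below the 5% of an interaction test. A pattern in one named direction has half the tabulated probability.

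It is tempting to say that a false phenotype-specific message would reach the guideline and care-pathway groups in section 8. That section discusses only a positive or negative study overall, so this is speculation.

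Finally, a statistical analysis plan may supply the interaction. That is possible, and the subgroup sentence does not rule it out. But the protocol itself fixes the contrasts by wheeze history and the multiplicity procedure, and states an interaction for another modifier. The gap therefore lies in choices this document makes, and is more than detail left for later.

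**Conclusion.** The point holds in a limited form. The protocol stratifies by wheeze history partly for insight into how the groups differ, yet states no test of whether the drug effect differs between them. Under the stated ANOVA gate and Tukey procedure, exactly one stratum is significant in about 14% of trials at a common 1-day effect, 26% at 1.36 days and 48% at 2.4 days. An interaction test would reject in 5%. The figures rest on an SD of 6 days, 99 evaluable per cell, normal outcomes, a four-cell ANOVA and identical true effects. The risk arises when there is a real common effect of roughly 1 to 3 days; with none it is about 2%. The overall comparison of azithromycin with placebo is unaffected. The change is worth making because the inviting misreading is easy to prevent.

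**What to change.** In section 6, Statistical Analysis:

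1. Add a drug by wheeze-history (first versus previous) interaction to the primary-outcome model, and report its estimate with a 95% confidence interval.
2. Keep the two within-stratum contrasts as tests or estimates of the effect in each stratum, with 95% confidence intervals.
3. State that any claim of differential response rests on the interaction estimate and its interval, not on one stratum being significant and the other not.
4. State the expected imprecision: about ±2.4 days, with 80% power only for a difference in effects of about 3.4 days.

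The cost is one model term and a few sentences, with no new patients or data. The downside is a more cautious subgroup conclusion. The protocol regards a one-day reduction as meaningful, and the interaction cannot resolve differences of that size. It will mainly prevent overclaiming and will seldom show how the groups differ.
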